Exclusion criteria will be applied as follows: (1) presence of other progressive skin diseases that may affect assessment of the condition; (2) treatment with the research drugs, biological agents, and immunosuppressive agents within 1 month before study initiation; (3) treatment with topical glucocorticoids and/or phototherapy within 2 weeks before study initiation; (4) presence of severe, uncontrolled, local or systemic, acute or chronic infection; (5) presence of severe systemic diseases, elevation of alanine aminotransferase or aspartate aminotransferase levels by > 1.5 times the upper limit of normal, elevation of creatinine by 1.5 times the upper limit of normal, decrease in any main blood test parameters (white blood cell count, red blood cell count, hemoglobin amount, platelet count) to below the lower limit of normal, or abnormalities in other laboratory test parameters; (6) history of malignant neoplasms, primary or secondary immune deficiency, and/or a hypersensitivity reaction; (7) major surgery within 8 weeks before study initiation or scheduled during the study period; (8) pregnancy or lactation; (9) history of alcohol abuse or drug abuse, family history of cancer, personal or family history of a serious mental illness; (10) any other factors considered by the researchers as contraindications for study participation.

Criteria for trial suspension, patient rejection, and patient withdrawal are also set as follows: (1) development of other serious or life-threatening organic lesions during the trial, (2) withdrawal at the individual’s discretion, (3) poor patient adherence to treatment, (4) participation in another trial administering treatment that may interfere with the results of the present study, (5) refusal to take contraceptive measures during the trial period (including both treatment and follow-up periods), (6) loss to follow-up for various reasons, and (7) incorrect application of the inclusion and exclusion criteria.

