### Sample size

In this study, the estimated post-treatment PASI score for all patients will be set at 50% lower than the pre-treatment score, both in the intervention group and the control group. The sample size of the current trial is calculated based on the following formula, and take the cure rate as the primary treatment effect index.
$$ n=\frac{p_1\times \left(1-{p}_1\right)+{p}_0\times \left(1-{p}_0\right)}{{\left({p}_1-{p}_0\right)}^2}{\left({z}_{\alpha /2}+{z}_{\beta}\right)}^2 $$

According to a previous study titled “Therapeutic Observation of Fire-needle Acupuncture for Stationary Plaque Psoriasis” [19], the cure rate to achieve this score is 76.8% for the intervention group and 35.3% for the control group. In this study, we set the inspection level (*α*) as 0.05, and the test power as 0.9, then *β* = 1–0.9 = 0.1. For two-sided tests, at least 25 participants would be required for each group. Considering the correlation of primary outcomes at different times and multicenter effect, we increase the sample size to 38 participants in each group, Considering a dropout rate of 20%, a total of 94 patients (47 per group) will be required for this study (Table 3).

**Table 3 Tab3:** Centers involved in a randomized trial evaluating fire needle therapy for blood stasis syndrome of plaque psoriasis

Research center	Sample size
Shaanxi Hospital of Traditional Chinese Medicine	20
Yueyang Hospital of Integrated Traditional Chinese and Western Medicine	20
First Affiliated Hospital of Heilongjiang University of Traditional Chinese Medicine	18
Affiliated Hospital of Jiangxi University of Traditional Chinese Medicine	18
Traditional Chinese Medicine Hospital of Shijiazhuang	18

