### Statistical analysis

A statistician will formulate a plan for statistical analysis in consultation with the PI. All analyses will be conducted using SAS statistical software, and the data network platform will be designed by the data management center of Nanjing Ningqi Medical Technology Co., Ltd., which will be entrusted with the third-party statistical analyses. The measurers will be blinded to the results. The overall principles will be as follows: An intention-to-treat (ITT) and per-protocol analysis will be used for statistical analysis. Quantitative variables (such as PASI, BSA, PGA, DLQI, PRQoL, VAS, and TCM syndrome scores) will be expressed as mean and standard deviation values or as median values with lower (Q1) and upper (Q3) quartiles. If the quantitative variables conform to normal distribution, a *t* test will be used (The homogeneity test will be performed for the two groups, with 0.05 as the significance level. The Satterthwaite method will be used to correct the *t* test when the variance is not uniform). If quantitative variables conform to skewed distribution, a nonparametric test will be used. Qualitative variables (such as cure rate, recurrence rate) will be expressed as numbers and percentages or composition ratios. Statistical inference will be performed using chi-square tests, Fisher’s exact tests, and Wilcoxon rank sum tests, among others. Potential confounding factors affecting the main outcome indicators will be adjusted by logistic regression. In this study, a *p* value of less than 0.05 is considered as statistically significant.

To account for missing data, we considered participants who may not complete the follow-up when calculating the sample size. The reasons, main characteristics, and data of a patient’s failure to follow-up will be recorded. Other types of randomly missing data will be considered unsuccessful according to the principle of ITT analysis.

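### The missing-data rule gives no value for a missing PASI score and leaves dropouts out, so the PASI comparison would be a completer analysis under an ITT label

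*Protocol article*

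**What the plan says.** All references are to the protocol article.

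- **Primary outcome.** Under Primary outcomes it is the decrease in PASI score. Statistical analysis lists PASI among the quantitative variables, to be compared by a t test or, if skewed, a nonparametric test. Sample size instead takes a cure rate as the main effect index: "the cure rate to achieve this score is 76.8% for the intervention group and 35.3% for the control group".
- **Analysis sets.** Statistical analysis promises ITT and per-protocol analyses and does not define them further.
- **Non-completers.** "To account for missing data, we considered participants who may not complete the follow-up when calculating the sample size". For these patients the plan is to record why they left, with their key features and data. No analysis rule follows.
- **Remaining missing data.** "Other types of randomly missing data will be considered unsuccessful according to the principle of ITT analysis".
- **Leaving the trial.** Inclusion and exclusion criteria has one undivided list, introduced by "Criteria for trial suspension, patient rejection, and patient withdrawal are also set as follows". It includes poor adherence, loss to follow-up and "incorrect application of the inclusion and exclusion criteria".
- **Data collection.** Table 2 schedules PASI at screening, at baseline, weekly during treatment, at early termination and at Weeks 6 and 8. The consent form asks whether data may be used after withdrawal. Under Secondary outcomes, a participant with confirmed recurrence may end follow-up.

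**The concern.** The only imputation rule in the plan does not fit the outcome that the plan makes primary. Failure is a category, and a t test or rank test on PASI change needs a number.

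The rule is also pointed at the less troublesome part of the missing data. Values missing at random are scored as failures, while dropouts, whose absence is more likely to be related to outcome, are met only by recruiting more patients. The protocol itself creates outcome-related missingness: recurrence is defined partly by PASI and can end follow-up.

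At stake is whether the PASI comparison keeps the protection of randomisation. With no rule for a missing PASI, the analyst following the text compares the patients who happen to have a value and reports the result as ITT.

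**Working it through.** **1. The plan's own sample size.** Inputs from Sample size: p1 = 0.768, p0 = 0.353, and "we set the inspection level (*α*) as 0.05, and the test power as 0.9". The plan's formula is n = [p1(1−p1) + p0(1−p0)] / (p1−p0)² × (z for α/2 + z for β)².

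- Numerator: 0.768×0.232 + 0.353×0.647 = 0.1782 + 0.2284 = 0.4066
- Denominator: 0.415² = 0.1722
- Multiplier: (1.960 + 1.282)² = 10.507
- n = 0.4066/0.1722 × 10.507 = 24.80, rounded up to 25

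This agrees with the plan: "For two-sided tests, at least 25 participants would be required for each group". The next step, "we increase the sample size to 38 participants in each group", is a factor of 38/25 = 1.52 with no stated derivation. The dropout step is 38/(1−0.20) = 47.5; the plan states 47 per group, 94 in total.

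**2. What the 20% allowance buys.** 47 × 0.80 = 37.6, so about 38 completers per group. The other 94 × 0.20 = 18.8, about 19 patients, are budgeted for but given no rule for a missing PASI.

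**3. The rule applied outcome by outcome.**

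| Outcome | Type in Statistical analysis | Does failure scoring give a value? |
|---|---|---|
| PASI decrease (primary) | quantitative | no |
| BSA, PGA, DLQI, PRQoL, VAS, TCM score | quantitative | no |
| Cure rate | qualitative | yes |

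**4. Why more patients do not help.** In arm k, let m_k be the fraction missing and d_k the mean PASI change of non-completers minus that of completers. The mean over all randomised patients is the completer mean + m_k·d_k. The completer difference (fire needle minus control) therefore misses the full difference by m0·d0 − m1·d1. With 20% missing in each arm this is 0.2 × (d0 − d1). The sample size does not appear in it, and equal dropout does not make it zero. The documents give no values for d0 and d1, so no figure for PASI can be put on it.

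**5. Where failure scoring can be computed: cure rate, illustration only.** Assumptions: the plan's rates are the true rates, every missing value is scored a failure, and missingness is unrelated to outcome. The splits by arm are assumed; the documents give none. Observed difference = 0.768(1−m1) − 0.353(1−m0). Power is the normal approximation at 47 per group, with pooled variance under the null.

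| Missing, fire needle / control | Rates | Difference | Power |
|---|---|---|---|
| 0 / 0 | 76.8% v 35.3% | 41.5 points | 99% |
| 20% / 20% | 61.4% v 28.2% | 33.2 points | 91% |
| 10% / 30% | 69.1% v 24.7% | 44.4 points | over 99% |
| 30% / 10% | 53.8% v 31.8% | 22.0 points | 58% |

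At 20%/20% the plan's formula gives [0.6144×0.3856 + 0.2824×0.7176]/0.332² × 10.507 = 41.9, so 42 per group instead of 25, before any increase for repeated times and centres.

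If the true cure rates were equal, a 30%/10% split in either direction would raise the two-sided rejection rate from 5% to about 12%, 17% or 34% for true rates of 35.3%, 50% or 76.8% (unpooled standard error, 47 per group). For 50%: rates 35% and 45%, standard error √[(0.2275 + 0.2475)/47] = 0.1005, shift 0.10/0.1005 = 0.99, rejection rate 17%.

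**6. The ITT set.** Statistical analysis promises ITT. The list under Inclusion and exclusion criteria allows rejection or withdrawal on grounds that arise or are noticed after randomisation. The two sections are never linked: neither says that the listed patients stay in the ITT set, and neither says that they leave it.

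**The case against.** The strongest reply is that failure scoring is conventional and computable for the cure rate, which Sample size calls the main effect index. On that view the real defect is the conflict between PASI decrease and cure rate, which is a separate point. This stands as far as the cure rate goes. It does not rescue the rule for PASI, which the Outcomes section designates as primary and Statistical analysis treats as quantitative. Even if the rule were meant to cover dropouts too, it would still supply no PASI value.

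A second reply is that the article gives only overall principles and that a statistical analysis plan will follow. Imputation detail may indeed be left to that plan. Here, though, a rule has already been fixed and labelled as ITT, and a later plan that followed it would inherit the mismatch.

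Four stronger readings are tempting, and the documents do not support them.

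- A reader might infer that rejected patients are removed from the ITT set. The text never says so. The listed grounds may be meant only for the per-protocol set, and the consent question on data use after withdrawal points towards keeping data.
- A reader might infer that early leavers have no usable PASI. Table 2 schedules PASI weekly and at early termination, and it does not say that later visits stop. What is missing is a statement of how these values enter the analysis.
- A reader might take the 22.0 to 44.4 point range as the bias in this trial. It rests on assumed splits. The 20% is the plan's dropout figure, whereas the plan's rule covers only other missing data, for which no rate is given. The same figures would arise under any analysis that scores all missing cure outcomes as failures, including the one recommended below. At equal 20% missingness, power at 47 per group stays at 91%, above the 90% target, if nothing is reserved for time and centre effects.
- A reader might assume that the heated needle causes more dropout. Both arms have the skin punctured, and all patients are told to expect mild pain. Unequal dropout is possible but undocumented.

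**Conclusion.** The point holds in a limited form. The stated rule cannot be applied to the stated primary outcome or to the other quantitative scores, and participants who do not complete follow-up have no analysis rule at all. Followed as written, the PASI comparison would rest on completers, about 38 of 47 per group at the planned dropout, while being called ITT. This conclusion rests on the text alone.

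The rejection list is an unreconciled risk to the ITT set, not a stated exclusion.

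The size of any bias in PASI cannot be computed from the documents. The cure-rate figures show only that failure scoring is sensitive to unequal missingness; they depend on the assumed splits and on missingness unrelated to outcome.

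**What to change.** 1. State that the ITT analysis includes all randomised patients as allocated, whatever ground for rejection or withdrawal applies, and that those grounds affect only the per-protocol set.
2. For PASI change, replace the rule with a mixed model for repeated measures. This has to be added, since the article names only t and nonparametric tests for quantitative variables. Use every observed visit, including the early-termination PASI assigned to the week in which it falls, under missing-at-random. Add a delta or tipping-point sensitivity analysis, because some follow-up may end on account of PASI itself.
3. Confine failure scoring to the cure rate and apply it to every missing value whatever the reason. Add multiple imputation as a sensitivity analysis, because failure scoring is itself sensitive to unequal missingness.
4. Keep collecting the assessments already scheduled from patients who stop treatment but have not withdrawn consent.

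Cost: wording in the protocol and analysis plan, slightly more analysis work, and attendance at visits that are already in the schedule. The downside is that an estimate that includes non-adherent patients may be smaller.

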## Discussion

The management of psoriasis has always been a focus of research in the field of dermatology. Dermatologists have continuously been exploring better ways to treat psoriasis, such as fish oil [20] and moving cupping therapy [5]. [name], a famous Chinese medicine practitioner, put forward the “new blood syndrome theory” based on the assumption that psoriasis is centered on “blood.” According to this theory, blood-heat occurs first, followed by blood-deficiency, blood-dryness, and blood-coldness. Blood-poison represents malignant development of disease, and blood-stasis is present throughout the course of the disease [21]. In light of Qin’s theory, blood-stasis can be caused by factors such as blood-heat and blood-dryness. This shows that the long-term existence of blood-stasis is the main pathological factor for the chronicity of psoriasis. The essence of BSS is reportedly a hypercoagulable state manifested by blood circulation and microcirculatory disorders [22].

Fire needle therapy is a special acupuncture treatment involving the use of needles and moxibustion [6]. When the heated needle penetrates the skin, it can improve the local microcirculation and regulate cell metabolism. The stimulation of acupoints in accordance with the meridian conduction pathways can resolve both internal and external discomfort and regulate the balance between yin and yang in the organs [23]. At the same time, the skin receives warm stimuli that also promote blood circulation [6]. Further, skin immunity plays a big role in the development of psoriasis. A study showed that patients with blood-heat syndrome of psoriasis vulgaris had substantially elevated levels of interferon-gamma, IL-17, IL-23, and TNF-α and significantly decreased levels of IL-4 and IL-10 [24]. According to our recent study and other studies, fire needle therapy can inhibit inflammatory reactions by inhibiting the abnormal proliferation of T cells (such as CD8+T cells) and reducing the number of IL-2 and IFNγ; in addition, it can increase the number of CD4+T cells, IL-4, IL-10 and the ratio of CD4+T cells and CD8+T cells; and also, it can promote the balance of Th1 and Th2 cells by reducing the number of Th1 cells and increasing the number of Th2 cells to improve the condition of psoriasis [25–27].

In China, fire needle therapy is listed as a special TCM therapy in the *Guideline for the diagnosis and treatment of psoriasis in China (2018 simplified edition)* [13]. However, to the best of our knowledge, there is no multicenter clinical study on the treatment of psoriasis with fire needle therapy. Moreover, research involving only basic treatments and fire needle therapy is scarce. Accordingly, the results of the proposed randomized controlled trial on the efficacy and safety of fire needle therapy for BSS of plaque psoriasis are expected to provide a high level of evidence.

### Trial status

This is version 3.0, and the protocol was registered at *clinicaltrials.gov* on May 15, 2019. Participant recruitment was initiated in June 2019 and is scheduled to be completed by the end of December 2020.

## Data Availability

The data and datasets analyzed during the current study are available from the corresponding author on reasonable request. Informed consent forms are also available from the corresponding author on request.

## Abbreviations

BSA: Body surface area
CRA: Clinical research assistant
CRO: Clinical research observer
DLQI: Dermatology Life Quality Index
PI: Principal investigator
IL: Interleukin
IRB: Institutional review board
ITT: Intention-to-treat
PASI: Psoriasis Area and Severity Index
PGA: Physician Global Assessment
PRQoL: Patient-reported quality of life
TCM: Traditional Chinese medicine
TNF: Tumor necrosis factor
SPIRIT: Standard Protocol Items: Recommendations for Interventional Trials
VAS: Visual analog scale
